### Project Phases and Study Design

3.1

Each phase of the project will use different quasi‐experimental designs. Table 1 presents a summary of the study design, population, setting, variables, sample size, and study period for each phase.

**TABLE 1 fsn371640-tbl-0001:** Study designs, study populations, study settings, study variables, sample size and estimated study periods for each phase of the project.

	Project phases			
	Phase 1	Phase 2	Phase 3	Phase 4
Study design	Three‐arm pre‐post parallel design	Four‐arm placebo‐controlled single‐blind pre‐post parallel design	Four‐arm placebo‐controlled single‐blind pre‐post parallel design	Two‐arm placebo‐controlled, single‐blind (participants), parallel feasibility trial
Study population	Healthy‐weight adults living in Australia	Healthy‐weight adults living in Australia	Overweight or Obese adults living in Australia	Overweight or Obese adults living in Australia
Study setting	Laboratory‐based	Laboratory‐based	Laboratory‐based	In a natural environment (at home)
Independent variable	Different MB doses (175, 350, and 700 mg)	Different MB doses (175, 350, and 700 mg) and placebo	Different MB doses (175, 350, and 700 mg) and placebo	MB or Placebo consumption in a natural environment
Dependent variable	Sour, bitter, tart, and sweet taste perception ratings of food‐based solutions and individual food items	Ratings for sourness and bitterness taste perceptions, overall liking and intake of hypo‐palatable mixed vegetarian salad Ratings for sweetness taste perceptions and overall liking of SSBs	As mentioned in Phase 2	Primary outcomes Food preferences (Overall meal liking and preferences across time) Energy intake Dietary quality Other outcomes of interest Feasibility of the treatment protocol and study procedures Appetite Anthropometry/Body composition
Sample size	54	40	40	30
Proposed study period	1 July–30 September, 2024	1 November 2024–30 September 2025	1 December–30 June, 2025	1 May–30 December, 2025

*Note:* Sociodemographic characteristics (sex*, age, income, employment status, and education status), phenotypic taste perception, genotypic taste sensitivity, mouth pH, anthropometry, and body composition will be collected as covariates. In Phases 3 and 4, comorbidities (e.g., diabetes, hypertension) and medication use (self‐reported) will also be assessed. In Phase 4, physical activity will be measured as a covariate for secondary outcomes. *Sex is classified based on biological characteristics.

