### Nutritional Profile of MB and Placebo Tablets

3.2

For this project, Sen Yuh Farm Science Co. Ltd., Taiwan (https://www.mberrytw.org) donated the MB and placebo tablets. MB tablets consisted of dried MB pulp (55%) and corn starch (45%) as a binding agent. Each tablet weighs 350 mg and contains approximately 0.16 mg of miraculin, according to the donor's report. This content of miraculin is within the range limit of 0.052%–0.32% used previously (Greenaway et al. 2024). The placebo tablets are composed of dragon fruit (20%) and corn starch (80%). Given concerns about the potential toxicity of synthetic food colorants and the corresponding recommendation to favor natural alternatives (Amchova et al. 2024; Malabadi et al. 2022), dragon fruit was incorporated into the placebo formulation to naturally match the color of the MB tablets and thereby support blinding. Table S1 presents the nutritional profile of the MB tablets provided by the donor organization, and the sugar analyses (glucose, fructose, sucrose, maltose, and mannose) of both MB and placebo tablets. Sugar analyses were conducted at the Queensland Alliance for Agriculture and Food Innovation (QAAFI), Centre for Nutrition and Food Sciences (https://qaafi.uq.edu.au/), using an in‐house method with high‐performance liquid chromatography (HPLC). As indicated in Table S1, the analysis indicated that the placebo tablets contained low levels of glucose and fructose, with no detectable sucrose, maltose, or mannose. This finding aligns with existing evidence showing that dragon fruit contains only minimal amounts of glucose and fructose and no detectable sucrose or maltose (Kakade et al. 2022; Tarte et al. 2023), while corn starch contains negligible sugar (Zhang et al. 2021). Therefore, the contribution of the 20% dragon fruit to the overall sugar content of the placebo tablets is considered minimal.

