**FIGURE 1 fsn371640-fig-0001:**
[figure not shown]
Phase 1 study design.

After the pre‐test, participants will drink water to neutralize their mouths. Group A will receive 175 mg (half a tablet), Group B will receive 350 mg (one tablet), and Group C will receive 700 mg (two tablets) doses in MB tablets. Subjects will be instructed to dissolve the tablet with saliva on their tongue for 5 min and make contact with the tablet against as much surface area of the oral cavity as possible without chewing or swallowing it (Hudson et al. 2018). Immediately after dissolving, participants will receive the same solutions and food items used for the pre‐test to capture changes in perceived taste perception on gLMS.

#### Phase 2

3.7.3

A hypo‐palatable vegetarian salad containing half‐serve vegetables (raw broccoli and rocket leaves) and half‐serve fruits (Granny Smith apple), which are the minimum possible servings per Australian dietary guidelines (Brownie et al. 2015), will be prepared 30 min before the data collection time at Griffith University, Gold Coast campus kitchen lab or the Participants' home, based on the participants' preferences. Food items for the vegetarian salad and the Coca‐Cola (representing hyper‐palatable SSB) will be purchased from the local market. The food will be stored in a refrigerator (4°C), removed, and placed on separate plastic trays 10 min before each test. The SSB will be kept at room temperature, and 30 mL will be poured into 50 mL paper cups, which are clean and uniform in color (Mielby et al. 2018).

Figure 2 shows that participants (*n* = 40) will be allocated to four treatment arms (*n* = 10 in each group). The data collection procedure will follow these steps:

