Initially, participants will review the participant information sheet and screening questions and sign a consent form. They will confirm (tick) the standardized instructions provided before their visit.Anthropometry measurements and body composition assessments will be conducted, and eligibility will be confirmed.For the TAS2R38 gene, saliva will be collected using the Oragene DNA OG‐500 kit as mentioned in Table 3.The pH of the mouth will be measured using a pH paper strip as mentioned in Table 3.Phenotypic taste sensitivity will be assessed by having participants place a PTC strip on the tip of their tongues.Rate their hunger level using the 10‐point hunger scale (0 = full, and 10 = very hungry), and assess their current mood status using a 10‐point mood scale (0 = happiness, and 10 = sadness).After rinsing their mouths with water, participants will receive a weighted vegetarian mixed salad. They will consume as much or as little from the given salad.Participants will rate the sourness and bitterness taste perception of the salad using gLMS, followed by their overall liking of the salad using the Labeled Affective Magnitude Scale (LAMS). The principal investigator will measure and record any leftover salad to measure their intake.After rinsing their mouths with water, participants will drink 30 mL of regular Coca‐Cola and rate its sweetness‐taste perception on gLMS and overall liking on LAMS.Participants will be required to wait for a compulsory 20‐min period after the pre‐testing procedures before commencing post‐testing. This interval is intended to allow hunger levels to return to baseline. The duration is based on the estimated energy content of the test meal (60 kcal, i.e., 251 kJ). Drawing on Horner et al. (2014), whose participants required approximately 3 h to recover from a ~1600 kJ meal, we calculated that ~23 min would be sufficient for our test meal; therefore, a minimum 20‐min waiting period will be adopted. As this duration may not fully account for individual differences in metabolism, dietary fiber intake, or the amount consumed during the pre‐test, participants will be verbally informed of the rationale for the interval and asked to notify the investigator once their hunger has returned to baseline. They will then be asked to complete the same hunger scale used upon arrival at the lab. If post‐waiting hunger ratings are comparable to baseline, the post‐test will proceed; otherwise, the waiting period will be extended until hunger levels return to baseline.According to their assigned group, participants will rinse their mouths and dissolve a given dose of MB (175, 350, 700 mg) or placebo (350 mg) in their mouth for 5 min.A vegetarian salad similar in content and amount to the one provided in the pre‐test will be provided. Participants will consume it as desired, and the principal investigator will measure and record any leftovers.Participants will rate the sourness and bitterness taste perception of the salad using gLMS, followed by their overall liking using LAMS.Finally, participants will rinse their mouths with water, drink 30 mL of regular Coca‐Cola, and rate the sweetness taste perception using gLMS and their overall liking using LAMS.

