2	To compare the effect of different doses of MB on sourness, and bitterness taste perceptions and overall liking of a hypo‐palatable mixed salad among healthy‐weight Australian adults	Different MB doses ○ Dose 1: ½ tablet (≈170 mg) ○ Dose 2: 1 tablet (≈350) ○ Dose 3: 2 tablets (≈700 mg) Placebo	Ratings for sourness and bitterness taste perception	gLMS (0–100)	As proposed in Phase 1 Additionally, as the sample size was determined using the empirical guideline of at least 10 subjects per predictor variable (Green 1991), and given the complexity in power estimation for mixed models, post hoc sensitivity power analysis will be conducted for planned comparisons. This will determine the minimum detectable effect size based on the achieved sample size and desired statistical power. Recent literature also recommends strengthening sample size justification for such approaches through sensitivity power analyses (Lakens 2022)
			Rating for overall liking	LAMS (0–100)	
			Intake	Served amount of salad minus left over	
	To compare the effect of different doses of MB on sweetness taste perceptions and overall liking of hyper‐palatable SSBs among healthy‐weight Australian adults	Different MB doses ○ Dose 1: ½ tablet (≈170 mg) ○ Dose 2: 1 tablet (≈350) ○ Dose 3: 2 tablets (≈700 mg) Placebo	Sweetness taste perception ratings	gLMS (0–100)	
			Ratings for overall Liking	LAMS (0–100)	
3	To compare the effect of different doses of MB on sourness and bitterness taste perceptions and overall liking of hypo‐palatable mixed salad among overweight or Obese Adults residing in Australia	Different MB doses ○ Dose 1: ½ tablet (≈170 mg) ○ Dose 2: 1 tablet (≈350) ○ Dose 3: 2 tablets (≈700 mg) Placebo	Ratings for sourness and bitterness taste perceptions	gLMS (0–100)	As proposed in Phase 2
			Ratings for overall liking	LAMS (0–100)	
	To compare the effect of different doses of MB on sweetness taste perceptions and overall liking of hyperpalatable SSBs among overweight/obese adults residing in Australia	Different MB doses ○ Dose 1: ½ tablet (≈170 mg) ○ Dose 2: 1 tablet (≈350) ○ Dose 3: 2 tablets (≈700 mg) Placebo	Ratings for sweetness taste perceptions	gLMS (0–100)	
			Ratings for overall Liking	LAMS (0–100)	

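### In Phases 2 and 3 the placebo has one amount (350 mg) while the miracle berry arms take half, one or two tablets, so tablet count can suggest active treatment and is confounded with dose

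*Protocol article*

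**What the plan says.** Table 1 (section 3.1) gives the same design for Phases 2 and 3: "Four‐arm placebo‐controlled single‐blind pre‐post parallel design". Section 3.7.3 allocates 40 participants, who "will be allocated to four treatment arms (*n* = 10 in each group"). In its tablet step the MB arms take 175, 350 and 700 mg, and the alternative is given as "or placebo (350 mg) in their mouth for 5 min". Section 3.7.4 applies the same procedure to Phase 3.

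Section 3.2 gives the MB tablet: "Each tablet weighs 350 mg and contains approximately 0.16 mg of miraculin". The tablet counts for the doses are in section 3.7.2 ("Group A will receive 175 mg (half a tablet), Group B will receive 350 mg (one tablet"; the 700 mg group takes two) and again for Phases 2 and 3 in Table 6, where the list ends "Dose 3: 2 tablets (≈700 mg) Placebo". Placebo has no count there.

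On matching, section 3.2 says that dragon fruit was used in the placebo to match the colour of the MB tablets in support of blinding. Section 3.7.5 adds similar size, participants seeing only their own tablets, and a treatment-guess question at the end, but for Phase 4. For Phases 2 and 3 the article describes no matching of the number of pieces and no check of blinding.

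**The concern.** A blinded placebo comparison needs participants in the compared arms to receive things that look alike and come in like quantity. Here quantity differs by arm. A participant who is handed a cut half or two tablets holds something that no placebo participant receives. If that participant knows or guesses that placebo is a single whole tablet, the count gives the allocation away. Even without that knowledge, being given less or more can set an expectation of a weaker or stronger effect.

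The Phase 2 and 3 outcomes are open to expectation: gLMS ratings of sourness, bitterness and sweetness, LAMS ratings of liking, and the amount of salad a participant chooses to eat. The purpose of these phases is to compare doses, and Table 6 plans pairwise comparisons across them. An expectation cue that moves with dose cannot be separated from the miraculin effect in the mixed model, because count and dose are the same variable among the MB arms.

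**Working it through.** **Inputs.** MB tablet weight 350 mg and about 0.16 mg miraculin (section 3.2); MB doses 175, 350 and 700 mg and placebo 350 mg (section 3.7.3); four arms of 10 (section 3.7.3); Phase 3 identical (section 3.7.4). Assumption: a placebo tablet also weighs about 350 mg. The article does not state this; it is inferred from the 350 mg placebo amount and from the similar tablet size described for Phase 4.

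**The plan's own figure.** 4 arms × 10 = 40 per phase, which agrees with Table 1.

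**Tablet count = amount / 350 mg.**

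| Arm | n | Tablets | Miraculin |
|---|---|---|---|
| MB 175 mg | 10 | 175/350 = 0.5 | 0.08 mg |
| MB 350 mg | 10 | 350/350 = 1 | 0.16 mg |
| MB 700 mg | 10 | 700/350 = 2 | 0.32 mg |
| Placebo 350 mg | 10 | 350/350 = 1 (assumed) | 0 |

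Table 6 gives the half tablet as about 170 mg where the text gives 175 mg. The two should be reconciled, but the count is half a tablet either way.

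**What the count tells someone who knows the scheme: P(active | count) = MB participants with that count / all participants with that count.**

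- Half a tablet: 10/10 = 1.00
- One tablet: 10/20 = 0.50
- Two tablets: 10/10 = 1.00
- If count carried no information: 30/40 = 0.75 for everyone

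So 10 + 10 = 20 of 40 participants per phase, and 40 of 80 over both, have a count that occurs only with active treatment.

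**Contrasts matched on count.** Of the three MB-versus-placebo contrasts, only 350 mg (10 against 10) is matched. The 175 mg and 700 mg contrasts are not. All three between-dose contrasts (175 v 350, 175 v 700, 350 v 700) differ in count as well as in miraculin.

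**Does inert mass add to the problem?** By the compositions in section 3.2, MB tablets are 45% starch and placebo tablets 80%. Starch is 0.45 × 175 ≈ 79 mg, 0.45 × 350 ≈ 158 mg and 0.45 × 700 = 315 mg in the MB arms, against 0.80 × 350 = 280 mg in placebo. The 700 mg arm is 35 mg from placebo, while the count-matched 350 mg arm is about 122 mg away. Starch does not follow the matched/unmatched pattern, and the fruit that rises with dose is the MB pulp itself, which is the intervention. The point therefore rests on the count and the total amount handed over, not on inert material.

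**The case against.** - **Participants may not know that placebo is one tablet.** This stands as a limit. The information sheet is not shown, and in a parallel design each person receives one allocation once, with no other count to compare. A reader might infer that half of each phase is in fact unblinded. The documents do not support that. They show a risk built into the design. The confounding of count with dose does not depend on what participants know.
- **A reader might extend this to the whole project.** That is not supported. Phase 1 has no placebo, and in Phase 4 both arms take at least two MB or placebo tablets daily (Table 2).
- **Seeing only one's own tablets protects the blind.** This safeguard is written for Phase 4 only. Even if applied in Phases 2 and 3, it hides differences in colour and not what the count conveys.
- **The taste change unblinds anyway.** This stands in part. The introduction says that MB consistently lowers sourness and raises sweetness of sour foods, and participants taste the same salad before and after the tablet. A noticeable effect could reveal any MB arm, including the 350 mg arm, so matching counts removes one cue only. But the count cue acts before tasting and could produce an apparent difference even if miraculin did nothing.
- **A full protocol may deal with this.** The point rests on a stated placebo amount and not on an omission. Placebo pieces added to the MB arms would alter the tablet step as it is written.

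**Conclusion.** The point holds for Phases 2 and 3 as a blinding and expectation risk. Placebo is given at one amount while the MB arms take half, one or two tablets. In each phase 20 of 40 participants receive a presentation that occurs only with active treatment, and two of the three placebo contrasts, plus every between-dose contrast, are confounded with tablet count.

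This rests on reading 350 mg of placebo as one tablet, and on taking single-blind to mean that participants are blinded, which Table 1 specifies for Phase 4 only. If the placebo tablet weight differs, the mismatch remains on amount: 175 mg and 700 mg still have no placebo counterpart. The size of any resulting bias cannot be computed from the document. It is a moderate weakness that is cheap to remove before data collection and cannot be repaired in the analysis afterwards.

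**What to change.** Leave the MB amounts as they are and change only the presentation.

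1. **Preferred.** Give all four arms the same number and size of pieces, filling up with placebo pieces. For example, with half-tablet pieces and four pieces per person, the 175, 350, 700 mg and placebo arms would contain 1, 2, 4 and 0 MB pieces and 3, 2, 0 and 4 placebo pieces. P(active) given the count is then 0.75 for everyone.
2. **Minimum.** Spread the ten placebo participants over the three tablet counts, 3 or 4 at each. With ten MB participants at each count, P(active) becomes 10/13 ≈ 0.77 or 10/14 ≈ 0.71. No count then identifies active treatment, but 3 or 4 per count give no useful count-matched contrast.
3. State the choice in the tablet step of section 3.7.3 and in Table 1, and state the placebo tablet weight.
4. Add the Phase 4 treatment-guess question at the end of each Phase 2 and 3 session.
5. If sessions are already complete, which the study periods in Table 1 make possible, limit the count-matched blinded claim to the 350 mg contrast and report the limitation for the others.

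**Cost.** For option 1, assuming 350 mg placebo tablets, placebo use per phase is 10 × (1.5 + 1 + 0 + 2) = 45 tablets instead of 10, so 35 more per phase, plus one or two protocol sentences. More inert material must dissolve in the same 5 minutes in the lower-dose and placebo arms. The added placebo material also varies inversely with MB dose: 525, 350 and 0 mg in the 175, 350 and 700 mg arms.

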
**FIGURE 2 fsn371640-fig-0002:**
[figure not shown]
Phases 2 and three study design.

#### Phase 3

3.7.4

The study design and data collection procedures followed in this phase are identical to those used in Phase 2 (Figure 2). They vary among study participants (Phase 2 is on healthy‐weight adults, and Phase 3 is on overweight or obese adults). A separate investigation is required because taste sensitivity alters with overweight and obesity (Harnischfeger and Dando 2021; Rohde et al. 2020; Vignini et al. 2019). Therefore, the dose of MB required to induce a change in taste perception and food liking may be different for overweight and obese adults than for healthy‐weight adults.

#### Phase 4

3.7.5

This will be a two‐arm, placebo‐controlled, single‐blind, parallel feasibility trial conducted over a 12‐week follow‐up period, in which participants will be blinded to group allocation. Blinding of participants will be maintained via the use of MB and Placebo tablets of similar size and closely matched colourings. Most importantly, participants will only receive their allocated treatment tablets and will not be privy to viewing the alternative treatment tablet. To minimize the risk of unblinding within households, only one participant per household will be enrolled. As this is a feasibility study, the success of blinding will also be evaluated by asking participants at the end of the trial whether they believed they had received MB or placebo.

The participants will have four visits to the Gold Coast campus, or they will be visited at their home by the principal investigator, based on their preference. That is, a first visit (at baseline), a second visit (at the end of the baseline week), a third visit (at the end of the 6th week), and a fourth visit (at the end of the 12th week). The main outcomes of interest are food preferences, energy intake, and dietary quality. Additionally, it will explore its effect on the overall liking of mixed meals (breakfast, lunch, dinner, and snacks) and on appetite. As it is a feasibility study, the other main outcomes of interest will be exploring the feasibility indicators (recruitment, blinding, allocation, retention, compliance, and adverse effects). Furthermore, as a secondary outcome, the study will investigate the effect of MB on anthropometry and body composition. Table 5 indicates the details of the study variables to be measured, including their frequency and the study visits at which they will be assessed.

**TABLE 5 fsn371640-tbl-0005:** Variables to be measured at each visit and throughout the follow‐up time of the Phase 4.

Variables to be measured at each visit	Intervention time and follow‐up duration													
	First visit	Second visit						Third visit						Fourth visit
	Day zero	Baseline week (week 0)	1st week	2nd week	3rd week	4th week	5th week	6th week	7th week	8th week	9th week	10th week	11th week	12th week
Sociodemographic characteristics (age, sex, income, educational status)	●													
Phenotypic taste sensitivity (using PTC strip)	●													
Food preferences using the Food Liking Questionnaire (FLQ)	●							●						●
Dietary quality using the Australian Recommended Food Score (ARFS)	●							●						●
Energy/food intake (using a 24‐h dietary recall)	●							●						●
Energy/food intake (using a 3‐day food record)^a^														
Overall liking of meals (breakfast, lunch, dinner, and snack), and appetite^b^														
Anthropometry	●							●						●
Body composition	●							●						●
Physical activity (IPAQ)	●							●						

^a^
The 3‐day dietary intake measurements will be supplemented with the 24‐h dietary recall method, conducted at baseline, midline, and end line. To measure dietary intake, participants will complete a 3‐day dietary intake record questionnaire within the marked week (on two weekdays and one weekend day).

^b^
Participants will record their overall liking of meals and their effect on their appetite on the Qualtrics survey link (or the hard copy version of it) throughout the 12‐week follow‐up. They will be requested to attach a photo of the meal tried with MB/placebo (both the meal served before eating and the leftover meal after eating).

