### Eligibility Criteria

3.3

The inclusion and exclusion criteria for all project phases are summarized in Table 2. Rubino et al. (2025) reported that Body Mass Index (BMI) alone is insufficient to define obesity, as it does not differentiate fat mass from lean mass. The recommendations are to confirm obesity through direct measurement of body fat where possible; otherwise, it should be defined as a high BMI combined with at least one additional adiposity indicator (waist circumference [WC], waist‐to‐height ratio [WHtR], or waist‐to‐hip ratio), or the presence of two such indicators irrespective of BMI. In line with this recommendation, we plan to use the WHO age‐, sex‐, and ethnicity‐specific cut‐offs (Barba et al. 2004; Li et al. 2023; Potter et al. 2024; WHO 2008). For this study, a healthy weight is defined as a BMI of 18.5 – 24.9 kg/m^2^ for Europeans and others, or 18.5 – 22.9 kg/m^2^ for Asian populations. Overweight/obesity is defined as a BMI ≥ 25 kg/m^2^ for Europeans and others, or ≥ 23 kg/m^2^ for Asian populations, together with at least one additional criterion: elevated WC (≥ 94 cm for men, ≥ 80 cm for women, ≥ 90 cm for Asian men), WHtR ≥ 0.5, or body fat percentage ≥ 25% for men or ≥ 35% for women, or meet at least two of the additional adiposity criteria. Detailed sex‐ and ethnicity‐specific cut‐offs to be used in Phases 3 and 4 are provided in Table S2.

**TABLE 2 fsn371640-tbl-0002:** Inclusion and exclusion criteria in each phase of the project.

Criteria	Phases 1 and 2	Phases 3 and 4
Inclusion criteria	Adults living in Australia Age 18–65 years Healthy weight BMI	Adults living in Australia Age 18–65 years BMI in the Overweight/Obesity category plus ○ High WC or high WHtR OR ○ High body fat percentage

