Exclusion criteria	Known alterations to the sense of smell and taste, including dysphagia SARS‐CoV‐2 infection within the last 3 months Food allergies or intolerances to berries. Current pregnancy or lactation (Turck et al. 2021) Self‐reported non‐communicable disease (Cancer, diabetes, hypertension, and chronic/acute liver disease or kidney problems)	All exclusions proposed for Phases 1 and 2 will apply, except those related to medical conditions. Participants with self‐reported cancer or chronic or acute liver or kidney problems will be excluded. However, those with other stable medical conditions (e.g., controlled diabetes, controlled hypertension, and other chronic diseases) will be eligible to participate in Phases 3 and 4. For Phase 4, as it is a follow‐up study requiring participants to take at least two MB/placebo tablets daily for 3 months, participants with existing medical conditions will be advised to consult their physician prior to confirming enrolment, in case they have unstable conditions (e.g., uncontrolled diabetes, uncontrolled hypertension, or other critical illnesses)

*Note:* Exclusion criteria are based on potential alterations to taste perception that may bias outcome assessment (Bernhardson et al. 2008; Boltong and Keast 2012; Brennan et al. 2020; Duffy 2020; Feng et al. 2014; Kanjanaumporn et al. 2020; Risso et al. 2020).

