### Participant Recruitment

3.5

Participants will be recruited using a convenience sampling technique. Recruitment will be advertised through Griffith University volunteer research broadcasts, social media platforms, and printed flyers displayed in various locations, including Griffith University premises (Gold Coast campus), medical centres, community centres, restaurants, places of worship, and leisure centres. Flyers will include the principal investigator's contact details (email) and a QR code for registration. In addition, recruitment strategies will include radio advertisements, direct in‐person/word‐of‐mouth approaches, and invitations to students enrolled in courses at Griffith University, Gold Coast campus. The recruitment plan is presented in Table S3.

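### Table 2 lists no exclusion for earlier-phase participation or prior miracle berry use, so re-enrolment from Phase 1 into 2 and Phase 3 into 4 is open and could weaken participant blinding

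*Protocol article*

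**What the plan says.** Section 3.3 states that "The inclusion and exclusion criteria for all project phases are summarized in Table 2". For Phases 1 and 2, Table 2 excludes altered smell or taste, recent SARS-CoV-2 infection, berry allergy or intolerance, pregnancy or lactation ("Food allergies or intolerances to berries. Current pregnancy or lactation") and self-reported non-communicable disease. For Phases 3 and 4, "All exclusions proposed for Phases 1 and 2 will apply, except those related to medical conditions". Neither column mentions earlier-phase participation or previous MB use.

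Section 3.5 describes one recruitment effort for the whole project: "Participants will be recruited using a convenience sampling technique". Its channels centre on one campus and the surrounding community, and are not separated by phase.

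In Phase 1 every participant takes MB and there is no placebo arm; for example, "Group C will receive 700 mg (two tablets) doses in MB tablets" (Section 3.7.2). Phases 2 and 3 each have three MB arms and one placebo arm of 10. The weight classes differ: "Phase 2 is on healthy‐weight adults, and Phase 3 is on overweight or obese adults" (Section 3.7.4).

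In Section 3.7.5, Phase 4 blinding rests on tablets of similar size and colour, on the statement that "participants will only receive their allocated treatment tablets and will not be privy to viewing the alternative treatment tablet", and on enrolling one person per household. Participants are asked at the end which product they think they had.

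**The concern.** MB has a recognisable effect: sour food tastes sweet. Someone who has had that experience knows what to look for, and someone given placebo later can notice that it is absent. Under the criteria as printed, a Phase 1 participant is eligible for Phase 2 and a Phase 3 participant for Phase 4. The household rule shows that the plan already limits enrolment to protect blinding. It covers two people in one home, but not one person across two phases.

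Many outcomes are self-reported: taste and liking ratings in Phases 2 and 3; food liking, meal liking, perceived appetite and food records in Phase 4. Participants who believe they know their arm may rate accordingly, which would most plausibly widen the MB-placebo difference. The Phase 4 end-of-trial guess, a feasibility indicator, would also partly reflect earlier exposure and not only how well the placebo works. No such guess is described for Phases 2 and 3.

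**Working it through.** **Which routes are open.** These follow from the Table 1 calendar and the weight criteria.

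- Phase 1 to Phase 2: both need healthy weight. Phase 1 ends 30 September 2024 and Phase 2 opens 1 November 2024. Open.
- Phase 3 to Phase 4: both need overweight or obesity. Phase 3 runs to 30 June 2025 and Phase 4 opens 1 May 2025. Open.
- Phases 1-2 to Phases 3-4: largely closed by weight class. A person could cross after a weight change, or through the Section 3.3 text, which defines healthy weight by BMI alone but also admits to the overweight/obese group those who "or meet at least two of the additional adiposity criteria". Table 2 instead requires a BMI in the overweight/obesity category. The two passages do not agree and must be reconciled.

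**Denominators.** The Phase 4 size reproduces from Section 3.4.3: 20 / (1 − 0.32) = 29.4, rounded up to 30; per arm 10 / 0.68 = 14.7, rounded up to 15.

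**Prior MB intake in the feeder phases.** Phase 1: 54/54 = 100%. Phase 3: 3 arms × 10 = 30 of 40 = 75%.

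**Illustration.** The documents give no re-enrolment rate. Let f be the assumed share of the later phase that comes from its feeder phase. Assume that returners reflect the feeder phase's arms in proportion, and that the new allocation is unrelated to the old one. Expected numbers with prior MB intake are then 40f in Phase 2 (10f of the 10 on placebo) and 30 × f × 0.75 in Phase 4 (15 × f × 0.75 of the 15 on placebo).

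| f (assumed) | Phase 2, of 40 | Phase 2 placebo, of 10 | Phase 4, of 30 | Phase 4 placebo, of 15 |
|---|---|---|---|---|
| 0% | 0 | 0 | 0 | 0 |
| 10% | 4 | 1 | 2.2 | 1.1 |
| 25% | 10 | 2.5 | 5.6 | 2.8 |
| 50% | 20 | 5 | 11.2 | 5.6 |

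**The alternative tablet.** With equal Phase 4 arms, the chance that a Phase 3 returner gets the other product is 0.75 × 0.5 (MB, then placebo) + 0.25 × 0.5 (placebo, then MB) = 0.5. About half of any returners would therefore fall outside the Section 3.7.5 assurance, whichever arm they were in during Phase 3.

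**The case against.** A reader might infer that carried-over knowledge unblinds Phases 2 to 4. The documents do not support that.

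- Phase 3 has no regular feeder phase, because the weight criteria separate it from Phases 1 and 2.
- Nothing says or implies that participants are re-used, so loss of blinding is a possibility and not a stated feature of the plan.
- Taking MB in Phase 3 is not the same as having felt its effect. Whether each dose produces a perceptible change in this group is the Phase 3 question. That phase is also single-blind, so someone on half a tablet may not know that they had MB.

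Three further objections have weight. First, this is an article. Section 3.7.3 mentions screening questions that are not shown, and the recruitment plan and the detail on feasibility indicators are in supplementary tables that are not shown, so a rule may exist there. Second, the tablets are closely matched, and a returner would compare from memory, not side by side. Third, people new to MB also get cues: lime is encouraged with the tablets in Phase 4, and the same foods are tasted before and after in Phases 2 and 3. Excluding experienced people would not remove those cues. Weighed salad intake and measured anthropometry are also less exposed than ratings.

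These points limit the size and certainty of the problem but do not remove it. Eligibility and blinding safeguards are fixed in this document, Table 2 is offered as the list for all phases, and the household rule was thought worth printing. The end-of-trial guess could detect a problem in Phase 4 but not prevent it.

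**Conclusion.** The point holds as a gap in the stated eligibility criteria. As written, they admit people who have already taken MB to single-blind placebo comparisons through two routes, Phase 1 to 2 and Phase 3 to 4. For a Phase 3 returner switched to the other product, the Phase 4 assurance about not seeing the alternative tablet would not hold.

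The number affected is unknown and may be zero; the table above is illustration only. With 10 placebo participants in Phase 2 and 15 in Phase 4, even a few experienced ones could matter. The direction of bias is plausible but not shown. The conclusion assumes that no screening rule outside the article already closes these routes.

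**What to change.** Add one exclusion to Table 2 for the placebo-controlled phases, mainly Phases 2 and 4: participation in an earlier phase of this project, or any previous use of miracle berry. Ask it among the existing screening questions. If such a rule already exists in the full protocol or screening form, print it in Table 2.

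If people with prior exposure are already enrolled, record it for each of them. Report the MB-placebo contrast, and in Phase 4 the blinding guess, with and without them.

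Reconcile the Section 3.3 wording on adiposity criteria with Table 2, so that it is clear whether anyone eligible for Phases 1-2 can also qualify for Phases 3-4.

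The cost is one line and one question. Planned sample sizes stay at 54, 40, 40 and 30. The downside is a slightly smaller recruitment pool.
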